**Objective:**

This prospective follow-up study aims to investigate early metabolic effects of initiating adjuvant endocrine therapy in women with estrogen receptor–positive early breast cancer and to compare conventional and expanded approaches to metabolic health classification.

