### Analytical Approach

Statistical analyses will be conducted using Stata (version 18.5), with a 5% significance level for hypothesis testing. Changes in continuous primary outcomes (BMI and MetS-*z* score) will be analyzed using linear regression or linear mixed-effects models, as appropriate, to estimate mean within-person changes from baseline to 3-month follow-up. Changes in secondary continuous outcomes, including the EMETA score and individual metabolic parameters, will be analyzed using similar regression-based approaches. Changes in categorical outcomes (MetS and Extended MetS prevalence) will be analyzed using logistic regression models.

To account for exposure heterogeneity and treatment-related confounding, type of ET (tamoxifen vs aromatase inhibitor) and prior cancer treatments with potential metabolic impact, including neoadjuvant or adjuvant chemotherapy and supportive corticosteroid use, will be included as covariates in all adjusted analyses.

To address the secondary research question of whether certain patients are more vulnerable to early metabolic health deterioration following the initiation of ET, exploratory subgroup analyses will be conducted across both primary and secondary outcomes. These analyses will examine whether metabolic changes differ according to baseline and treatment-related characteristics, including age, BMI category, baseline metabolic status, menopausal status, type of ET, prior chemotherapy, smoking status, and comorbidity score. These subgroup analyses will be considered hypothesis-generating. Missing data will be assessed for randomness and extent. If data are missing at random, appropriate methods such as multiple imputation or mixed-effects models will be applied. Sensitivity analyses will be conducted to evaluate the potential impact of missing data on the study’s primary and secondary outcomes.

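### Because everyone starts endocrine therapy, the planned treatment covariates, as described, do not account for treatment-related confounding of the primary mean change

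*Protocol article*

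**What the plan says.** The Objective is to "investigate early metabolic effects of initiating adjuvant endocrine therapy". Study Population and Exposure make clear that all 112 participants initiated ET, and no group without ET is described.

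Under Analytical Approach, BMI and the MetS z score "will be analyzed using linear regression or linear mixed-effects models, as appropriate", the target being "to estimate mean within-person changes from baseline to 3-month follow-up". The same section names ET type and earlier cancer treatments, "including neoadjuvant or adjuvant chemotherapy and supportive corticosteroid use, will be included as covariates in all adjusted analyses". The reason given is "To account for exposure heterogeneity and treatment-related confounding".

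The section names no visit-by-treatment term, reference level or standardised contrast for the adjusted change. Apart from this adjustment, prior chemotherapy appears there as one of eight characteristics for exploratory subgroup analysis. The limitations in the Discussion are the single centre, the exclusion of diabetes, informative dropout and the modest sample size. They mention neither the lack of a comparator nor recovery from earlier treatment.

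**The concern.** Where exposed and unexposed patients are compared, a covariate controls confounding by balancing the two groups. Here ET initiation is the same for every woman. It has no coefficient apart from the passage of time, and no covariate can be associated with it. What threatens the primary estimate is metabolic change over the same 3 months with another cause, such as recovery after chemotherapy or steroids. The article itself describes these treatments as potentially metabolic in their impact.

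If the covariates do not act on the mean change, the adjusted result for both primary outcomes repeats the unadjusted one. A report could then present it as an ET effect from which treatment-related confounding has been dealt with. ET type is a separate matter: it is a version of the exposure, so it can modify the change but cannot confound it.

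**Working it through.** **Inputs from the article.** n = 112; SD of BMI change 3 kg/m² (Cohort Size, from a study over 3 to 5 years); detectable change 0.8 kg/m²; 5% significance level, taken as two-sided because the article does not say.

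**1. The plan's own figure.** SE = 3/√112 = 0.283. Power = Φ(0.8/0.283 − 1.96) = 80.6% by the normal approximation (79.9% by noncentral t). The stated power above 80% is reproduced, and this point does not affect it.

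**2. Mixed model, covariates as main effects.** Let y_it = α + βt + γ′x_i + u_i + e_it, with t = 0, 1. Within a woman, y_i1 − y_i0 = β + (e_i1 − e_i0), so γ′x_i cancels. With complete pairs the estimate of β is the crude mean change. Check in one simulated cohort: visit coefficient 1.0746 (SE 0.277) both with and without the covariates, and crude mean change 1.0746.

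**3. Change regression read at cohort means.** Let d_i = a + b′(x_i − x̄) + e_i. Least squares gives a = mean of d_i, again the crude mean change.

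**4. Change regression read at a chosen level.** Let d_i = a₀ + b₁·chemotherapy_i + b₂·steroids_i + … With two visits, b₁ is the visit-by-chemotherapy effect. With ET type centred, a₀ is the mean change in women with neither treatment. This quantity does respond to the adjustment.

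**5. Illustration.** Assumed values, not from the article: true ET effect 0; non-ET BMI change of 0.8 in women given chemotherapy; chemotherapy share 20, 40 or 60%; steroids in 90% of those women and in no others; aromatase inhibitor in 60% of women with and 75% without chemotherapy; drift common to all women of 0 or 0.3; SD of change 3. There were 1,000 cohorts of 112 per row. "Adjusted" covers steps 2 and 3, and SE is the SD across cohorts.

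| Common drift | Chemotherapy share | Crude | Adjusted | No chemotherapy, no steroids | SE crude | SE last estimate |
|---|---|---|---|---|---|---|
| 0 | 20% | 0.167 | 0.167 | 0.005 | 0.283 | 0.315 |
| 0 | 40% | 0.343 | 0.343 | 0.025 | 0.291 | 0.381 |
| 0 | 60% | 0.484 | 0.484 | 0.002 | 0.295 | 0.448 |
| 0.3 | 20% | 0.458 | 0.458 | 0.292 | 0.281 | 0.318 |
| 0.3 | 40% | 0.627 | 0.627 | 0.305 | 0.286 | 0.360 |
| 0.3 | 60% | 0.775 | 0.775 | 0.294 | 0.273 | 0.453 |

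The largest difference between crude and adjusted in any cohort was about 2 × 10⁻¹³. By hand, the expected crude value without common drift is share × 0.8 = 0.16, 0.32, 0.48, in line with the table. The estimate of step 4 drops the chemotherapy part and keeps the common drift.

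**6. Precision of the step 4 estimate.** Women without chemotherapy number 112 × (1 − share) = 89.6, 67.2, 44.8. SE = 3/√n = 0.317, 0.366, 0.448, or 1.12, 1.29 and 1.58 times 0.283. The change detectable with 80% power, (1.96 + 0.84) × SE, is 0.89, 1.02 and 1.25 kg/m², against 0.79 for the whole cohort.

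**The case against.** The best defence has four parts.

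- **A permitted model can do it.** The article allows linear regression, and a regression of change carries the visit-by-chemotherapy effect as its chemotherapy coefficient. This stands. A reader might infer that the adjusted analyses contain no such term at all, and the article does not support that. What is open is which contrast from that model counts as the adjusted change.
- **Centring and reference levels belong in an analysis plan that is not shown.** This stands for the detail. A reader might also infer that a raw intercept for a woman of age 0 would be reported. Nothing in the article says so, and its stated target is the mean within-person change. But the article goes beyond leaving detail open: it says what the covariates achieve, and for that target they do not achieve it.
- **The covariates are useful elsewhere.** This stands. In comparisons of change between patients, such as by ET type or menopausal status, prior chemotherapy and steroids can be genuine confounders. The wording is also to account for confounding, not to remove it.
- **The equality needs complete pairs.** This stands. With missing follow-up, covariates can move the visit estimate and make a missing-at-random assumption more plausible. That addresses dropout, not recovery from earlier treatment. The algebra also concerns the linear models for the primary outcomes, not the logistic models for MetS prevalence.

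The planned subgroup analysis by prior chemotherapy would show stratum-specific changes, but it is labelled hypothesis-generating and does not define the adjusted primary estimate.

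**Conclusion.** The point holds in limited form, as a should-fix. For the mean change in BMI and the MetS z score, with complete pairs, the listed covariates return the crude change when they are main effects in a mixed model or are read at cohort means in a change regression. The stated purpose regarding treatment-related confounding is then not met for the primary estimate. The equality is algebraic and does not depend on assumed values.

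The size of any resulting distortion is unknown. The article gives no chemotherapy share and no recovery effect, so 0.17 to 0.48 kg/m² is an illustration under assumed inputs, and the true direction could differ. A reader might infer that the primary results are shown to be biased. They are not: the article's claim to have dealt with one source of bias is what lacks support. Nor would the supporting estimate isolate ET, because non-ET change common to all women remains in it.

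**What to change.** 1. Keep the cohort mean change as the primary estimate and call it descriptive. Centring covariates at cohort means is a reasonable way to report it, but it removes no confounding.
2. For BMI and the MetS z score, include visit-by-prior-chemotherapy and visit-by-corticosteroid terms, or use the equivalent change regression. Prespecify the change in women without prior chemotherapy or steroids as a supporting estimate.
3. In Analytical Approach, limit the claim to describing heterogeneity of change and to adjustment of between-patient comparisons. Treat ET type as a possible modifier, not a confounder.
4. Word conclusions as change during the first 3 months of ET. Add to the Discussion limitations that there is no non-ET comparator, so non-ET change common to all women cannot be separated.

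The cost is plan wording and a few model terms. The treatment data are already collected (Covariables), and analysis was scheduled only after follow-up ended. A comparator can no longer be added, which is why item 4 is needed. The supporting estimate is less precise: its SE is about 1.1 to 1.6 times that of the cohort mean if 20 to 60% of women had chemotherapy (assumed range).

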### Measurements

The screening procedures included biometric measurements and blood sample collections. The biometric measurements were height, weight, hip and waist circumference, and blood pressure. Non-fasting venous blood samples were analyzed for HbA_1c_, plasma glucose, hemoglobin, total cholesterol, triglycerides, LDL, HDL, and circulating estradiol.

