#### Covariables

Information on the following co-variables has been collected from medical records and will be included in adjusted analyses. These include patient demographics: age, weight, height, Carlson Comorbidity score (0, 1‐2, 3‐4, ≥5), current comorbidities (none, cardiopulmonary disease, neurological, dyslipidemia, musculoskeletal, other cancers, abdominal, urogenital, endocrine, dermatological, others), smoking status (never smoker, former smoker, active smoker), civil status (living alone, living with a partner), and area of living (rural/city). Cancer-specific characteristics: date of breast cancer diagnosis, disease stage (T+N), human epidermal growth factor receptor 2 status, histological type, grade of malignancy, and previous breast cancer history. Treatment modalities included duration and type of neo-adjuvant and adjuvant therapy (including supportive prednisolone treatment), date of breast cancer surgery, and radiotherapy.

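### Comparing change in metabolic scores by baseline metabolic status builds in regression to the mean, so the contrast cannot show which women are vulnerable to ET

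*Protocol article*

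**What the plan says.** Analytical Approach sets a secondary research question, "whether certain patients are more vulnerable to early metabolic health deterioration following the initiation of ET", and answers it with subgroup comparisons: "exploratory subgroup analyses will be conducted across both primary and secondary outcomes". These are to "examine whether metabolic changes differ according to baseline and treatment-related characteristics, including age, BMI category, baseline metabolic status", among others; baseline metabolic status and BMI category are two of the eight subgroup variables listed. The same section adds a caution: "These subgroup analyses will be considered hypothesis-generating".

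The models for continuous outcomes are linear regression or linear mixed models, used "to estimate mean within-person changes from baseline to 3-month follow-up". MetS and extended MetS prevalence go to logistic regression.

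Study Design gives one screening at baseline and one at 3 months. Under Measurements, "Non-fasting venous blood samples were analyzed", which covers the glucose and triglycerides that enter every score. Under Study Population, everyone enrolled was starting ET.

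The Covariables section lists what enters adjusted analyses: "These include patient demographics: age, weight, height, Carlson Comorbidity score", followed by clinical and treatment items. It names no baseline MetS-Z, EMETA, lipid, glucose or blood pressure term. The limitations in the Discussion do not mention regression to the mean.

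**The concern.** Change is follow-up minus baseline. If a woman's baseline glucose, triglycerides or blood pressure happened to be high that day, the same fluctuation pushes her towards the unhealthy group and pushes her change downwards. A chance low value does the reverse. The grouping variable and the outcome thus share the baseline fluctuation with opposite sign, so the groups drift towards each other even if nobody's underlying level moves. Non-fasting sampling adds meal-related variation to two of the five components.

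A group not starting ET would show the same drift, and it could be subtracted. None is described. The risk is a report that metabolically healthy women deteriorate most after starting ET, when the pattern is partly or wholly an artefact.

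**Working it through.** **The plan's own figure.** Cohort Size states power above 80% for a BMI change of 0.8 kg/m² with SD 3 and n = 112. Taking a two-sided 5% level: 0.8 × √112 / 3 = 2.822; 2.822 − 1.960 = 0.862; Φ(0.862) = 80.6%. This reproduces. It concerns the whole-cohort mean change, not the subgroup contrasts.

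**Inputs for the artefact.** From the documents: n = 112, one baseline and one follow-up visit, MetS as at least 3 of 5 thresholds, the MetS-Z formula, 5% level. Assumed, because the documents give none: retest correlations, component means and SDs, and a correlation between components of 0.25. Baseline metabolic status is taken to mean MetS at baseline, the most natural reading of a term the article does not define.

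**Direction and formula.** With no true change, equal variances at both visits, retest correlation ρ, and a fraction p above cut-point c on the outcome itself:

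- expected change above the cut = −(1 − ρ) φ(c) / p
- expected change below the cut = +(1 − ρ) φ(c) / (1 − p)

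For p = 0.30 and ρ = 0.7, φ(c) = 0.3477. This gives −0.3 × 0.3477 / 0.30 = −0.35 SD above the cut and +0.3 × 0.3477 / 0.70 = +0.15 SD below it. The signs hold for any ρ below 1.

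**MetS-Z change by baseline MetS, simulated with no ET effect.** About 21% of women have MetS at baseline.

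| Retest correlation of MetS-Z | Mean change, no MetS | Mean change, MetS | Difference | False result: healthy worsen more |
|---|---|---|---|---|
| 0.79 | +0.16 | −0.60 | 0.76 | 43% |
| 0.85 | +0.11 | −0.43 | 0.54 | 31% |
| 0.91 | +0.07 | −0.26 | 0.33 | 20% |

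A separate simulation under other assumed settings gave 14% to 28%. The combined range is 14% to 43%. A sound two-sided 5% test would give 2.5% in that direction.

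**Effect of baseline adjustment.** With follow-up MetS-Z regressed on continuous baseline MetS-Z plus status, two-sided false rejection of the status term falls to about 5% to 7%.

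**MetS itself.** Here the problem is structural: women without MetS can only gain it and women with MetS can only lose it. In one simulated setting prevalence is stable at 20.6% and 20.8%, yet 11.2% of women without MetS gain it and 42.1% of those with MetS lose it. The flows balance: 0.794 × 0.112 = 8.9% of the cohort in, 0.206 × 0.421 = 8.7% out. In a second setting the proportions are 9.6% and 36.1%, again with stable prevalence.

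**BMI category.** Assuming baseline BMI with mean 26 and SD 5, and no ET effect, for non-obese minus obese women:

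| Assumed SD of 3-month BMI change | Spurious difference (kg/m²) | False result: leaner women worsen more |
|---|---|---|
| 0.5 | 0.04 | 6% |
| 1.0 | 0.18 | 12% |
| 1.5 | 0.39 | 19% |

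With baseline weight and height in the model the difference is about 0 and false rejection about 5%. For MetS-Z change by BMI category the difference is 0.00 and the false rate in that direction 2.5%.

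**The case against.** **The analyses are exploratory.** They are labelled hypothesis-generating, and the Discussion concedes limited power for subgroups. That limits the consequence. The label guards against chance findings and multiplicity, however, and does not remove a bias of known direction.

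**The model is not fully fixed.** The article neither specifies nor excludes a baseline-outcome term in the subgroup models, and a fuller plan may contain one. This stands: a reader might infer that the planned analysis must give a wrong answer, and the text does not support that. One permitted form is biased; another largely is not. Choosing a mixed model does not settle it, because a visit-by-status interaction estimates the same raw-change contrast.

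**The size depends on the split.** A reader might apply figures from cutting the continuous outcome at its own top quartile, where false-positive rates reach about 87%, 70% and 41% at retest correlations of 0.7, 0.8 and 0.9. The article names no such split, and its own MetS definition gives about half that or less.

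**BMI category is not equally affected.** A reader might group it with metabolic status. The calculations do not support this, and weight and height are already listed for adjusted analyses.

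**The direction is not certain in the real data.** A true ET effect concentrated in unhealthy women could mask or reverse the artefact. This also stands: the bias is one of expectation under no effect.

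**Conclusion.** The concern holds for one subgroup variable, baseline metabolic status, against MetS-Z, EMETA, MetS, extended MetS and their components. In those comparisons a raw-change contrast is biased towards showing healthy women worsening and women with MetS improving. Without a comparator it cannot be separated from an ET effect. In the MetS-Z simulations the false finding arises in roughly 14% to 43% of studies against 2.5%. That range rests on assumed retest correlations and component distributions; the direction under no effect does not, provided retest correlation is below 1.

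It does not extend to the whole-cohort mean changes in the primary outcomes, which do not depend on this grouping, or to the six subgroup variables other than metabolic status and BMI category. BMI category is a minor matter for BMI change and about nil for MetS-Z. The point should be corrected before analysis, but it concerns one exploratory contrast and does not threaten the study's main results.

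**What to change.** 1. For outcomes sharing components with baseline metabolic status, do not compare raw change, or a visit-by-status interaction, across status groups. Model the follow-up value conditional on the continuous baseline value of that outcome, or drop the contrast.
2. For MetS and extended MetS, report new-onset and resolved cases side by side.
3. State regression to the mean as a limitation, and do not read baseline-status contrasts as vulnerability to ET. Baseline adjustment removes the spurious step between groups; without a comparator it still does not identify who is vulnerable.
4. Keep the other subgroup variables, including BMI category. When BMI is the outcome, carry baseline BMI, or baseline weight and height, in the model.

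The cost is analysis wording only: no new data are needed, and one exploratory subgroup result is replaced or reworded.

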Metabolic health is traditionally assessed using MetS, a dichotomous classification that identifies individuals as metabolically unhealthy when at least three of five criteria are met: hypertension (blood pressure ≥130/85), hypertriglyceridemia (triglycerides >2 mmol/l), low HDL (HDL <1.295 mmol/l), central obesity (waist circumference >88 cm), or hyperglycemia (plasma glucose >7.8 mmol/l) [19]. However, this binary approach may overlook subtle or early metabolic changes that do not meet clinical thresholds. [19,20]. An established alternative is the Metabolic Syndrome *z* score (MetS-*z* score), a continuous composite measure of standardized MetS components and widely used in research to assess metabolic health along a continuum [21-24]. However, both MetS and MetS-Z omit several cardiometabolic indicators relevant to breast cancer survivorship, including low-density lipoprotein (LDL), hemoglobin A_1c_ (HbA_1c_), BMI, and waist-to-hip ratio (WHR) [13,25,26]. To address this limitation, this study introduces two expanded measures of metabolic health, for exploratory and hypothesis-generating purposes: An extended MetS definition and the EMETA score, a dichotomous classification and a composite *z* score using the same approach as the MetS-*z* score, both incorporating the extended metabolic variables.

The aim of this study is to evaluate the early impact of initiating adjuvant endocrine therapy on metabolic health in women with ER+ EBC and to compare conventional and expanded approaches to classify metabolic health.

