### Cohort Size

The study aimed to include 112 participants over the six-month enrollment period. The target was based on an annual referral rate of approximately 360 patients to the Department of Oncology, AUH, for adjuvant systemic therapy, of which approximately 90% were eligible for ET due to ER+ EBC, and assuming a 70% participation rate among eligible patients.

Statistical power calculations supported the sample size. Based on a comparable study with a similar population [30], where the standard deviation of the change in BMI over 3‐5 years after diagnosis was 3, a cohort of 112 participants provides >80% power to detect a true change in BMI of 0.8 kg/m^2^ at a 5% significance level. Furthermore, other studies have found larger BMI changes over shorter periods. For instance, Heideman et al observed a mean BMI change of 2.0 kg/m^2^ (± 4.9) after one year, with 26% of patients gaining ≥5 kg following adjuvant treatment [31].

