### Statistical Analysis

#### Definition of Analytic Values

BMI will be calculated as weight (kg)/height^2^ (m). WHR will be calculated as waist circumference divided by hip circumference. Blood pressure will be calculated as the average of three measurements. Middle arterial pressure will be calculated as 2 times diastolic blood pressure added systolic blood pressure divided by 3.

MetS will be defined as meeting at least three of five criteria: hypertension (blood pressure ≥130/85), hypertriglyceridemia (triglycerides >2 mmol/l), low HDL (HDL <1.295 mmol/l), central obesity (waist circumference >88 cm), or hyperglycemia (plasma glucose >7.8 mmol/l) (Figure 2).

Extended MetS will be defined as meeting at least 3 of the five criteria: hypertension (blood pressure ≥130/85), hypertriglycemia (triglycerides >2 mmol/l or LDL >3 mmol/l), low HDL (HDL <1.295 mmol/l), adiposity (waist circumference >88 cm, BMI ≥30, or WHR >0.85), or hyperglycemia (plasma glucose >7.8 mmol/l or HbA_1c_ ≥42 mmol/mol).

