## Results

The study was funded in July 2024. Participant recruitment occurred from November 2024 through April 2025, during which 112 of 166 eligible patients were enrolled. Among the 54 eligible patients who were not enrolled, 18 declined participation, 26 were not informed of the study by their treating practitioner, and 10 elected not to initiate adjuvant ET. All enrolled participants completed baseline assessments, and follow-up data collection was completed in September 2025. No deviations from the approved study protocol occurred, and no protocol amendments were made following ethical approval. Data cleaning and statistical analyses are scheduled to commence in February 2026, with dissemination of the final study results anticipated in July 2026.

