## Discussion

This study is anticipated to indicate that initiation of ET in women with ER+ EBC will be associated with modest early metabolic changes over the first three months of treatment. These changes may include small increases in BMI and selected lipid-related parameters, while markers with longer biological response times, such as HbA_1c_, may show minimal or no short-term change. Extended and continuous measures of metabolic health may capture early alterations not identified by conventional MetS definitions. Importantly, these analyses are exploratory and intended to evaluate sensitivity and feasibility rather than to establish clinical thresholds or predictive value.

Previous studies have linked ET with weight gain, insulin resistance, and dyslipidemia, all of which increase cardiovascular risk and may impact breast cancer outcomes [5,10-12,14,32]. However, most prior work has focused on longer-term outcomes or relied on dichotomous classifications. By evaluating both conventional and expanded measures within a short-term framework, this study contributes to understanding how early metabolic changes may be characterized following ET initiation.

Key strengths of this study include its prospective design with paired baseline and 3-month follow-up data, allowing within-subject comparison of early metabolic changes. The use of both conventional and expanded metabolic measures enables comparison of different classification approaches and addresses known limitations of binary definitions. The short follow-up period and alignment with routine clinical care minimize additional participant burden, supporting broad inclusion and reducing the risk of selection bias related to study participation.

The study is conducted at a single center, which may limit generalizability beyond similar healthcare settings. Exclusion of patients with pre-existing diabetes, while necessary to reduce baseline metabolic confounding, restricts applicability to a population that commonly receives endocrine therapy. In addition, although efforts were made to minimize attrition, informative dropout cannot be excluded, particularly if early metabolic or treatment-related symptoms influenced follow-up participation. The modest sample size limits power for subgroup analyses, which are therefore considered exploratory.

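### Effect modification by BMI is planned by category; adding a continuous-BMI test is a cheap gain for an exploratory analysis with limited power

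*Protocol article*

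**What the plan says.** Under Analytical Approach, exploratory subgroup analyses are to show whether some patients are more vulnerable to early metabolic deterioration, across primary and secondary outcomes. The characteristics are given as "including age, BMI category, baseline metabolic status, menopausal status, type of ET, prior chemotherapy, smoking status, and comorbidity score". BMI carries the word category; age does not. Neither the number of BMI categories nor their cut-points are given. The BMI threshold of 30 in the article belongs to the extended metabolic measures, for example "adiposity (waist circumference >88 cm, BMI ≥30, or WHR >0.85" in the extended MetS definition, and is not linked to the subgroups.

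The same section adds: "These subgroup analyses will be considered hypothesis-generating". The Discussion adds: "The modest sample size limits power for subgroup analyses, which are therefore considered exploratory".

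Exact baseline BMI will be in the data. Weight and height are measured at screening (Biometric Measurements), BMI is computed from them (Definition of Analytic Values), and the Results section says that all enrolled participants completed baseline assessments.

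**The concern.** Grouping treats women at BMI 25.1 and 29.9 as alike and women at 29.9 and 30.1 as different (with a cut at 30). If the change in an outcome rises or falls steadily with BMI, the variation within each group is discarded and the test for a gradient weakens. With 112 women, and power already acknowledged as limited, a real gradient in MetS-Z, lipids or blood pressure would be missed more often. In hypothesis-generating work that has a cost, because a gradient that is not seen raises no hypothesis for a later study.

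**Working it through.** **The plan's own figure.** Cohort Size states: "after diagnosis was 3, a cohort of 112 participants provides >80% power to detect a true change in BMI of 0.8" kg/m². The standard error is 3/√112 = 0.283, and 0.8/0.283 = 2.82. Two-sided power is Φ(2.82 − 1.96) = 80.6% (79.9% by paired t). The stated power reproduces. It concerns the mean change in the whole cohort and says nothing about modification by BMI.

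**Inputs for the modifier.**
- From the article: n = 112 ("112 of 166 eligible patients were enrolled") and a 5% level ("with a 5% significance level for hypothesis testing"), taken as two-sided.
- Assumed, because not given: baseline BMI normal, mean 25-28, SD 4-5.5; the cut-points; a linear effect of 0.27 residual SD of the outcome change per SD of BMI; no dropout. The slope was chosen to give about 80% power with continuous BMI.

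**Information kept.** Under a linear effect, the share kept is k = Var(E[BMI | category]) / Var(BMI) = Σ pᵢmᵢ², where pᵢ is the share in category i and mᵢ its mean in SD units from the cohort mean.

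Example with mean 27 and SD 5:
- Cuts at 25 and 30: p = 0.345, 0.381, 0.274 and m = −1.069, 0.092, 1.215. So k = 0.394 + 0.003 + 0.405 = 0.802, a loss of 20%.
- Single cut at 30: p = 0.726, 0.274 and m = −0.459, 1.215. So k = 0.153 + 0.405 = 0.558, a loss of 44%.

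**Power.** For continuous BMI, R² = 0.27²/(1 + 0.27²) = 0.068. For a category scheme, f² = kR²/(1 − kR²) and the noncentrality of the F test is 112f².
- Continuous: 112 × 0.0729 = 8.16, power 81%.
- Three groups, 2 df: kR² = 0.802 × 0.068 = 0.0545, f² = 0.0576, noncentrality 6.45, power about 60%.
- Cut at 30, 1 df: kR² = 0.558 × 0.068 = 0.0379, f² = 0.0394, noncentrality 4.42, power about 55%.

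Over the assumed range of means and SDs:

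| Form of BMI | Information lost | Power |
|---|---|---|
| Continuous, linear | 0% | 81% |
| Cuts 25/30, unordered | 19-25% | 57-61% |
| Cuts 25/30, 1-df trend | 19-25% | 68-72% |
| Single cut at 25 | 36-48% | 52-61% |
| Single cut at 30 | 39-65% | 38-59% |
| Cuts 18.5/25/30, unordered | 12-18% | 55-58% |
| Cuts 18.5/25/30/35, unordered | 9-15% | 51-55% |

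Four or five groups keep more information, but in an unordered test the extra degrees of freedom use it up. A lognormal BMI (mean 26, SD 4.5, or mean 27, SD 5) gives losses of 20% for cuts at 25 and 30, 40-44% for a cut at 25 and 40-47% for a cut at 30.

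**If the effect is not linear.** A simulation with BMI mean 26.5 and SD 5, and a step of 0.6 SD exactly at BMI 30, reverses the order: 48% power for the linear term, 65% for three groups and 76% for the cut at 30.

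**The case against.** The strongest reply is that the comparison is set up for the linear term to win: the effect is assumed linear and the slope is chosen to suit it. That is fair, and the step scenario shows that categories can do better. Neither form is best for every shape, so categories are not without benefit. What stands is that a step exactly at the chosen cut would need a rationale, and the article offers none.

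Second, category definitions and the form of an exploratory test are commonly left to an analysis plan, which is not shown. The absence of cut-points is therefore no fault. The choice of a category, however, is written down, and cut-points set later would still follow from it. A trend test across categories would recover about half of the lost power, but not all.

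Third, Covariables lists weight and height among the adjustment variables, without bands, so body size may already enter as continuous. That does not isolate a gradient in BMI: the two enter separately, and in a mixed model with main effects only they do not describe change.

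A reader might also infer that the plan contradicts itself, since the Introduction says of MetS that "this binary approach may overlook subtle or early metabolic changes that do not meet clinical thresholds". That sentence is about a dichotomous outcome missing change over time. It makes no claim about grouping a baseline modifier, so the parallel is one of reasoning and not a contradiction. Nor does the article say that age will be grouped.

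**Conclusion.** The point holds as a low-priority improvement. The article names a category for a modifier that is measured exactly, in analyses whose power it describes as limited. Under a roughly linear effect, and a test that ignores order, every scheme examined costs about 20 or more points of power at n=112; a trend test across three groups costs about 10.

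A reader might want to attach one loss figure to this plan. The documents do not support that: without cut-points or a BMI distribution, the loss runs from 9% to 65% across plausible schemes, and every value depends on the assumed distribution and on linearity. It would also be too strong to say that the vulnerability question is invalidated. The analyses are labelled hypothesis-generating, no primary estimate depends on them, and a gradient of the assumed size would be missed about one time in five even with continuous BMI.

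**What to change.** Add one sentence to Analytical Approach: modification by BMI will be tested with baseline BMI as a continuous variable (linear, with one spline check), predicted change will be reported at selected values such as BMI 22, 27 and 32, and BMI categories will be used for descriptive display only.

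This needs no new data and little analyst time. The drawback is that a linear term is less sensitive than categories if the true effect is a step at a cut-point; the spline check and the descriptive category table cover that. The article schedules analysis from February 2026. If it has begun, the continuous analysis can still be added and labelled as an addition.
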